### Refinement of the algorithm during daily life use to reduce false positives [DETECT-3]

False positive cardiac arrest alarms experienced during daily life will be assessed in the DETECT-3 study. It is a prospective observational study in adult volunteers (n=∼300). The study population consists of the following groups: 1) Adult (healthy) volunteers in different age groups: 18–29 years, 30–39 years, 40–59 years, 60–79 years, 80 + years old; 2) Patients with a history of cardiac disease.

Participants will wear the CardioWatch 287-2 to continuously record PPG and accelerometry signals for a period of two months (at least 960 recording hours), and are asked to keep an activity diary. At the end of the study, usability will be evaluated by the Usability Metric for User Experience (UMUX), Net Promotor Score (NPS) and Autonomy and Competence in Technology Adoption (ACTA) questionnaires.^17^, ^18^, ^19^, ^20^

The collected data from the wristband will be analysed afterwards to assess the false positive cardiac arrest alarm rate using the algorithm developed in DETECT-1. After each group of 25 participants completes the study, the algorithm will be refined to reduce the false positive rate in the next iteration. This refinement includes modifications to the PPG-algorithm as well as the incorporation of accelerometer data into the cardiac arrest detection model. The false positive alarm rate (primary endpoint) is defined as the number of false positive alarms per 40 days (960 recording hours).

The PPG data from 200 participants (eight iterations of 25 participants each; ∼192,000 recording hours) will be used to train and adapt the algorithm for false positive alarms. Through software adaptations, we aim to halve the number of false positive alarms per iteration of 25 patients (covering at least 24,000 recording hours). The final set of included patients (approximately 100) will be used for algorithm validation.

### Validation of the entire CA detection system [DETECT-4]

#### DETECT-4a

DETECT-4a is designed to test the performance of the developed cardiac arrest detection model − which now integrates both PPG and accelerometer data − in simulated cardiac arrest scenarios, providing final optimization and validation. It is a simulation study in healthy adult volunteers (n=∼50) in whom we simulate cardiac arrest by two steps, while wearing the CardioWatch (model 287-2/287-3). First, a circulatory arrest will be simulated by inflating a blood pressure cuff on the same arm as where the wristband is applied. Second, sudden falls mimicking cardiac arrest related-collapses will be performed by the participant immediately after circulatory arrest induction (at least eight simulated collapses per person). The simulated collapses will either be sudden or gently, from standing, sitting, and lying positions.

The collected PPG and accelerometry data will be used for the final optimization of the previously developed cardiac arrest detection model using iterations of ten participants each (at least 80 simulated cardiac arrest events per iteration), until a sensitivity of at least 95% is reached, with a maximum of four iterations (i.e. 40 participants; at least 320 simulated events). Subsequently, prospective testing will be performed in a final subset of ten participants with at least 80 simulated arrests. Considering the non-normal distribution of the sensitivity estimate, the Wilson 95% CI is approximately 0.93–0.98 with a margin of error of ± 5%.

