### PPG-algorithm development and validation in a hospital setting [DETECT-1]

#### DETECT-1b

The DETECT-1b provides external validation of the PPG-algorithm developed in DETECT-1a. The workflow of the PPG-algorithm has previously been described.^13^ DETECT-1b is a prospective multicentre study in patients with shockable cardiac arrest, conducted in four university medical centres in the Netherlands. Adult patients (*n* = 50) in whom short-lasting cardiac arrest is induced as part of routine practice during subcutaneous implantable cardioverter defibrillator (S-ICD) implantation or ventricular tachycardia (VT) ablation are eligible for inclusion. Study participants will be equipped with a PPG wristband (CardioWatch 287-2) during the procedure. As reference standards, continuous ECG and arterial blood pressure data will be collected. All events of induced ventricular fibrillation (VF) or pulseless VT, defined as a mean arterial pressure ≤ 45 mm Hg and/or pulse pressure ≤ 15 mm Hg, are regarded as cardiac arrest events. The primary endpoint is the sensitivity for cardiac arrest detection. Secondary endpoints are the positive predictive value and false positive cardiac arrest alarms.

Based on an anticipated event rate of 60% and a 98% sensitivity observed in DETECT-1a, we determined a required sample size of approximately 50 patients is required to achieve an accurate estimate of sensitivity. Using a 95% Wilson confidence interval (CI), we obtained a range of 0.833 to 0.994 with a margin of error of approximately 8%.

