### Accelerometry algorithm development [DETECT-2]

DETECT-2 is a prospective study to develop and validate an accelerometry-based algorithm for detection of sudden falls mimicking cardiac arrest related-collapses in healthy adults (*n* = 20). Each study subject will be instructed to perform a series of fall movements on a safety mat, while wearing the CardioWatch. The falls include falls forward (from a standing position or while walking), backward, sideways, and softer falls, such as sliding off a chair or against a wall. After each fall, the participant will be instructed to lay still for at least 20 s, like in a collapse resulting from cardiac arrest. The fall movements are based on previous studies investigating videotaped sudden cardiac death.^14^, ^15^, ^16^ In addition, the participants will be instructed to perform a predefined set of activities of daily living (ADL), which will be annotated as non-fall data.

Accelerometry signals will be recorded. Video recordings from the study area will be used as a reference standard. Based on the accelerometer data, a machine learning model will be developed for the detection of the sudden falls, with a 70% training set and 30% test set. Primary endpoint is the sensitivity of the accelerometry algorithm for detection of sudden falls. Secondary endpoints include false positive fall alarms and the sensitivity to detect soft falls.

The sample size will be 20 individuls, yielding a total of 400 sudden fall events (20 events per included subject), 200 soft fall events (ten per participant), and 800 simulated non-fall events (nine different types of ADLs per included subject, performed multiple times). Targeting a sensitivity of 95% for sudden fall detection, 400 sudden fall events allow estimation of sensitivity with a margin of error of approximately 2.2% (Wilson 95% confidence interval 0.946–0.967).

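### The planning margins for DETECT-4a (±5%) and DETECT-2 (2.2%) count repeated falls by the same person as independent, so they are too narrow under any positive within-person correlation

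*Protocol article*

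**What the plan says.** **Protocol article, section DETECT-4a.** Each volunteer contributes "at least eight simulated collapses per person". The model is tuned in groups of ten "until a sensitivity of at least 95% is reached, with a maximum of four iterations". After that, "prospective testing will be performed in a final subset of ten participants with at least 80 simulated arrests". The precision claimed for this final test is "the Wilson 95% CI is approximately 0.93–0.98 with a margin of error of ± 5" percent.

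**Protocol article, section Accelerometry algorithm development [DETECT-2].** Twenty healthy adults perform scripted falls, "yielding a total of 400 sudden fall events (20 events per included subject". The claimed precision is "400 sudden fall events allow estimation of sensitivity with a margin of error of approximately 2.2% (Wilson 95% confidence interval 0.946–0.967". The same section develops the model "with a 70% training set and 30% test set".

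Neither section mentions correlation between falls by one person, a design effect or an interval adjusted for participants.

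**The concern.** A Wilson interval on an event count assumes that each event carries independent information. Here one person supplies eight or twenty events. In DETECT-2 the way a person falls and how the band sits on the wrist are shared across that person's falls. In DETECT-4a the same holds, with the band and cuff on the same arm throughout. If some people are systematically harder to detect, misses collect in those people, and 80 or 400 events carry less information than the count suggests.

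The number of people is small: ten in the DETECT-4a test and twenty in DETECT-2. DETECT-4a is the last check of the combined model before its use at home by ICD patients, and the Discussion sets a sensitivity goal above 90–95% and calls the sample sizes sufficiently large. A margin that ignores clustering makes that goal look better secured than it is.

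**Working it through.** **Inputs**
- DETECT-4a: 80 events, 10 people, m = 8 per person (the stated minimum). Sensitivity p = 0.95 is an assumption: the section gives 95% as the tuning target and names no other value for the interval.
- DETECT-2: 400 sudden falls, 20 people, m = 20, p = 0.95 as stated.
- ICC: not in the article. A range of 0.05 to 0.3 is assumed.

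**Formulas**
- Wilson centre: (p + z²/2n) / (1 + z²/n)
- Wilson half-width: z·√[p(1−p)/n + z²/4n²] / (1 + z²/n), with z = 1.96
- Effective sample size: n_eff = n / [1 + (m−1)·ICC], put into the Wilson formulas in place of n

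**Step 1: the article's own figures, every event independent**
- DETECT-4a, n = 80: centre (0.95 + 0.0240)/1.0480 = 0.929, half-width 0.051, interval 0.878–0.980. The ±5% and the upper limit 0.98 reproduce; the lower limit 0.93 does not.
- DETECT-2, n = 400: centre (0.95 + 0.0048)/1.0096 = 0.946, half-width 0.022, interval 0.924–0.967. The 2.2% and the upper limit 0.967 reproduce; the lower limit 0.946 does not.

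Both margins therefore match a design effect of exactly 1. The printed lower limits equal the Wilson centres (0.93 and 0.946 after rounding), so it appears that the centre was printed where the lower limit belongs. That slip has nothing to do with clustering.

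**Step 2: allow for clustering**

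| Study | ICC | Design effect | n_eff | Wilson 95% interval | Half-width |
|---|---|---|---|---|---|
| DETECT-4a (10 × 8) | 0 | 1 | 80 | 0.878–0.980 | 5.1% |
| | 0.05 | 1.35 | 59 | 0.862–0.983 | 6.0% |
| | 0.1 | 1.7 | 47 | 0.847–0.985 | 6.9% |
| | 0.3 | 3.1 | 26 | 0.794–0.989 | 9.8% |
| DETECT-2 (20 × 20) | 0 | 1 | 400 | 0.924–0.967 | 2.2% |
| | 0.05 | 1.95 | 205 | 0.911–0.972 | 3.1% |
| | 0.1 | 2.9 | 138 | 0.900–0.976 | 3.8% |
| | 0.3 | 6.7 | 60 | 0.863–0.983 | 6.0% |

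**Step 3: DETECT-2 on the test set only**

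Thirty percent of 400 is 120 falls. The article does not say whether the split is within people or between people.
- Independent: half-width 4.1%.
- Split within people (20 × 6): design effect 1.25 to 2.5, n_eff 96 to 48, half-width 4.6% to 6.8%.
- Split by people (6 × 20): design effect 1.95 to 6.7, n_eff 62 to 18, half-width 5.9% to 12.1%.

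**The case against.** **These are planning statements.** A reader might infer that the final 95% intervals will cover the true sensitivity too rarely. Beta-binomial simulation at p = 0.95 shows what would happen if an unadjusted Wilson interval were used: at ICC 0.1 and 0.2, coverage is 86% and 78% for 10 × 8, and 76% and 63% for 20 × 20. But the article does not say that the final analysis will be unadjusted, and the analysis plan is not shown. Only the published planning margins can be faulted.

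**The ICC is assumed.** This stands. Fall types also vary within each person, and misses driven by the type of fall rather than by the person would not widen the interval in this way. Wrist perfusion is no argument for DETECT-2, which uses only the accelerometer, and is a weak one in DETECT-4a, where a cuff stops the flow. The direction under any positive ICC is certain; the size is not.

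**Much of the visible gap in DETECT-4a is not clustering.** A reader might put the whole distance from the printed 0.93 down to clustering. The arithmetic slip alone accounts for about 5 points (0.93 to 0.878). Clustering adds 1.6 points at ICC 0.05 and 3.1 at ICC 0.1.

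**DETECT-1b.** A reader might extend the point there, because "All events of induced ventricular fibrillation (VF) or pulseless VT" meeting the pressure criteria count as arrests. The documents do not support this. The stated 0.833–0.994 is exactly Wilson for 29/30, and 30 = 50 × 0.60, which fits one event per patient. If each of those 30 patients had m events, n_eff = 30m/[1 + (m−1)·ICC], which is never below 30 for an ICC up to 1; two events each at ICC 0.3 gives 60/1.3 = 46. The interval would be too narrow only if the 30 events came from fewer than 30 patients, which the article does not say. The handling of repeat inductions can be left to the analysis plan.

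**Conclusion.** The point holds for the planning precision of DETECT-4a and DETECT-2, and only for that. The stated margins rest on every fall being independent.

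At an assumed ICC of 0.05, the half-width rises from 5.1% to 6.0% in DETECT-4a and from 2.2% to 3.1% in DETECT-2 on all 400 falls. At 0.3 it reaches 9.8% and 6.0%. The DETECT-2 figure is larger again if sensitivity is estimated on the test set alone.

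These sizes depend on the assumed ICC, equal numbers of events per person, p = 0.95 and the effective-n approximation. The wrong lower limits need correcting whatever view is taken of the ICC. The documents do not show that the DETECT-1b interval is too narrow or that the final analyses will be unadjusted.

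**What to change.** - Restate the DETECT-4a and DETECT-2 margins over a stated ICC range using n/[1 + (m−1)·ICC], and say whether the DETECT-2 margin refers to all 400 falls or to the test set, and how that set is split.
- Correct the independence limits to 0.878–0.980 (DETECT-4a) and 0.924–0.967 (DETECT-2).
- Report the final sensitivity with an interval that allows for clustering by participant.
- For DETECT-4a, use a small-sample method such as Wilson on the effective sample size, with the ICC or its source fixed beforehand. A percentile bootstrap over ten participants is not a safe choice: with about four misses expected (5% of 80), its simulated coverage was about 87%, 84% and 77% at ICC 0.05, 0.1 and 0.2, no better than the unadjusted Wilson interval (90%, 86% and 78%), and it collapses to a point when there are no misses. With 20 people and 20 falls each it does better (90% against 76% at ICC 0.1).

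The cost is in wording and in wider stated intervals. No further participants or data are required.

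### DETECT-4a: the stated Wilson interval of 0.93–0.98 contradicts its own ±5% margin; at 95% sensitivity with 80 events it is about 0.88–0.98

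*Protocol article*

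**What the plan says.** The protocol article, section DETECT-4a, has each volunteer perform "at least eight simulated collapses per person". The detection model is optimised in groups of ten participants "until a sensitivity of at least 95% is reached, with a maximum of four iterations", which is at most "40 participants; at least 320 simulated events". After that, "prospective testing will be performed in a final subset of ten participants with at least 80 simulated arrests". The precision statement follows directly: "the Wilson 95% CI is approximately 0.93–0.98 with a margin of error of" ± 5%. That sentence names the method and the confidence level, but not the sensitivity assumed.

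The section on DETECT-2 has a comparable statement for 400 sudden falls at a targeted sensitivity of 95%: "margin of error of approximately 2.2% (Wilson 95% confidence interval 0.946–0.967".

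**The concern.** The sentence conflicts with itself before any recalculation. From 0.93 to 0.98 is 5 points in total, so the half-width is 2.5 points, while the margin is given as ± 5%. Elsewhere the article uses the margin of error as a half-width. DETECT-1b pairs 0.833–0.994 with about 8% (half-width 8.05 points), and DETECT-4b pairs 74–99% with ± 12% (half-width 12.5 points). By that usage, either the interval or the margin in DETECT-4a is wrong.

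What is at stake is how precise the test set appears to be. The Discussion says that missing an arrest is not acceptable in the intended users, so readers will look first at the lower limit. If the lower limit is the wrong figure, the planned precision looks about twice as good as it is.

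**Working it through.** **Inputs**
- n = 80 events: ten participants with at least eight each (DETECT-4a). This is a minimum.
- p = 0.95: the optimisation target in the same paragraph. It is inferred, because the interval sentence does not state it.
- z = 1.96, so z² = 3.8416.

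**Formulas (Wilson score interval)**
- centre = (p + z²/2n) / (1 + z²/n)
- half-width = z·√[p(1−p)/n + z²/4n²] / (1 + z²/n)

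**Attempt to reproduce the DETECT-4a figure (76/80)**
- 1 + z²/n = 1 + 3.8416/80 = 1.04802
- centre = (0.95 + 0.02401) / 1.04802 = 0.9294
- half-width = 1.96·√(0.00059375 + 0.00015006) / 1.04802 = 0.0510
- interval = 0.9294 ± 0.0510 = **0.878 to 0.980**

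The upper limit (0.98) and the margin (± 5%) agree with the article. The lower limit (0.93) does not. It equals the centre, and 0.929 + 0.051 = 0.980, so the printed interval appears to run from the centre to the upper limit.

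**Could another input give 0.93–0.98?**

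| Detected of 80 | Wilson 95% interval | Half-width |
|---|---|---|
| 75 | 0.862–0.973 | 0.056 |
| 76 | 0.878–0.980 | 0.051 |
| 77 | 0.896–0.987 | 0.046 |
| 78 | 0.913–0.993 | 0.040 |
| 79 | 0.933–0.998 | 0.033 |
| 80 | 0.954–1.000 | 0.023 |

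Counts from 70 to 74 give lower limits of 0.785 to 0.846. No count out of 80 gives 0.93–0.98.

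- *Other methods at 76/80:* the lower limit is 0.870 for Wilson with continuity correction, 0.877 for Clopper–Pearson and 0.886 for Jeffreys. The Wald interval is 0.95 ± 0.048, or 0.902–0.998. None gives 0.93.
- *More events at 95%:* 320 events give 0.920–0.969 and 500 give 0.927–0.966. The upper limit falls below 0.98 as the lower limit rises.
- *More events at 96%:* 240 events give 0.927–0.978 and 320 give 0.933–0.977. These are close to 0.93–0.98, but the half-widths are 2.6 and 2.2 points, which contradicts ± 5%.

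**Same check on DETECT-2 (n = 400, p = 0.95)**
- 1 + z²/n = 1.009604
- centre = (0.95 + 0.004802) / 1.009604 = 0.9457
- half-width = 1.96·√(0.00011875 + 0.0000060025) / 1.009604 = 0.0217
- interval = **0.924 to 0.967**

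The article prints 0.946–0.967 with a margin of 2.2%. Again the upper limit and margin are right, and the centre stands where the lower limit should be.

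**A correct example.** In DETECT-1b, 29/30 gives a Wilson interval of 0.833–0.994 with half-width 0.080, exactly as printed. The slip therefore does not affect every interval in the article.

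**The case against.** The arithmetic leaves little room for dispute. The strongest objections concern the inputs and the consequence.

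*The inputs are a floor and a minimum.* The interval sentence does not name 95%, and 80 is the least number of events. This is true, so the corrected interval has to be stated as conditional. It does not rescue the printed figure: of the counts out of 80, only 76 gives both an upper limit of 0.98 and a margin of 5%, and the conflict between interval and margin needs no input at all.

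*The interval is only approximate.* Rounding cannot explain a 5-point shift in an interval about 10 points wide.

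*The correct margin is already there.* A reader who relies on ± 5% has the right precision, and nothing in the design depends on the lower limit. This stands and limits the weight of the point.

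*Stronger readings that the article does not support.* A reader might infer that the plan claims to exclude sensitivities below 93%, or that the corrected interval shows the test set failing a goal of more than 90%. DETECT-4a sets no hypothesis or success rule on a confidence limit; its 95% criterion only ends optimisation. The aim in the Discussion of sensitivity above 90–95% describes the whole programme and is not tied to a lower limit. DETECT-4b plans for 74–99%. A slightly better result would also change the picture: 78/80 gives 0.913–0.993.

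**Conclusion.** The DETECT-4a precision statement is wrong as printed. Its interval contradicts its margin, and at 76/80 the lower limit is 0.878, not 0.93, about 5 points less favourable. Substituting the Wilson centre for the lower limit is the likely cause; this is an inference, supported by the same pattern in DETECT-2, where the lower limit should be 0.924 and not 0.946.

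The internal contradiction rests on no assumption. The value 0.878 assumes 95% sensitivity, exactly 80 events and independence between events. Each participant contributes eight or more events, so independence may be favourable. As an illustration only, with assumed intraclass correlations of 0.05, 0.10 and 0.20 (not in the article) and an effective number of events of 80/(1 + 7·ICC) = 59.3, 47.1 and 33.3, the lower limit would be about 0.86, 0.85 and 0.82. The finding does not depend on this.

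For the same reason, it would go too far to say without conditions that the test set excludes sensitivities below 88%. That holds only for 76/80 detected with independent events.

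**What to change.** In DETECT-4a, replace the interval with wording such as: *assuming 76 of 80 simulated arrests are detected (95%) and treating events as independent, the Wilson 95% CI is approximately 0.88–0.98, half-width about 5%*. Add no unconditional statement about which sensitivities the test set rules out, and do not imply that the lower limit must exceed 90%.

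In DETECT-2, correct the interval for 400 falls at 95% to 0.924–0.967; the 2.2% margin stays.

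The cost is one corrected sentence in each section. Sample size, endpoint and analysis are unchanged. The only loss is that the stated lower limits become less favourable.

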#### DETECT-4b

The DETECT-4b study is a prospective multicentre observational cohort study in which the complete cardiac arrest detection system will be validated in ICD-patients (*n* = ∼200) during daily life use. The cardiac arrest detection system consists of the cardiac arrest detection algorithm integrated into the CardioWatch 287-3 wristband and includes test alerting to the dispatch centre.

Adult patients with an ICD for secondary prevention and patients with an ICD for primary prevention who have received at least one time appropriate ICD therapy are eligible for inclusion. Participants will wear the CardioWatch 287-3 for one to two years. The primary endpoint is the sensitivity for the detection of a first episode of cardiac arrest. Secondary endpoints are the positive predictive value, false positive alarms per user year, day-level specificity, and sensitivity for the detection of all cardiac arrest events. A cardiac arrest event is defined as appropriate ICD therapy in combination with (short-lasting) loss of consciousness, transient loss of consciousness with a ventricular arrhythmia in the monitoring zone or discharge diagnosis of presumed ventricular arrhythmias below the ICD monitor/detection zone, or true death. Intracardiac electrogram recordings in combination with clinical reports will be used as reference standard. Usability will be studied using the UMUX, NPS and ACTA questionnaires.^17^, ^18^, ^19^, ^20^

The presumed incidence of cardiac arrest events (as defined above) is expected to be 8% per year.^21^, ^22^ Given an expected median follow-up duration of 1.5 years and assuming a true sensitivity of 95%, a sample of approximately 200 patients is needed to achieve this sensitivity with a 95% Wilson confidence interval ranging from 74% to 99%, corresponding to a margin of error of ± 12%. Since the number of sampled non-events is substantially larger, specificity can likewise be confirmed with sufficient power. The DETECT-4b is registered at ClinicalTrials.gov (NCT06692374).

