In the DETECT-4 studies, the complete cardiac arrest detection system will be tested. This includes evaluating the connection between the bracelet and the dispatch centre. When a cardiac arrest is detected, the bracelet will emit an acoustic alarm and alerts the dispatch centre in case of a non-cancelled alert. Despite all these efforts, the false alarm rate will not be reduced to zero. False positive alerts are also observed in systems like crash detection in cars and crash or fall detection in smartwatches and smartphones,^23^ but must be minimized to avoid unnecessary ambulance dispatches. While false alarms are a concern, automated cardiac arrest detection can also contribute to more accurate alerts. It is known that EMS dispatchers can sometimes misinterpret the presence or absence of cardiac arrest during phone assessments.^24^, ^25^ Therefore, automated cardiac arrest detection not only has the potential to serve as first witness but can also confirm or correct a human-reported cardiac arrest.

The DETECT program distinguishes itself from other initiatives by prioritizing patient data over simulated data and using sufficiently large sample sizes to ensure a robust scientific foundation for the technology.^10^, ^11^, ^12^ The goal is to achieve high sensitivity (>90–95%) to minimize the risk of missing a cardiac arrest diagnosis, while keeping false positives low to support feasible implementation. The design of the DETECT program encompasses all necessary steps for the development, validation, and testing of cardiac arrest detection technology. The successive studies will yield comprehensive insights into the factors influencing its accuracy guiding further development. Once available, post-implementation and effectiveness studies need to be conducted to provide evidence of the value of wearable-based cardiac arrest technologies in improving patient outcomes.

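### DETECT-4b: the printed interval for sensitivity (74% to 99%, ±12%) does not follow from the printed inputs, which give about 23–24 first events and about 78% to 99% (±10%)

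*Protocol article*

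**What the plan says.** The Protocol article, section DETECT-4b, takes the sensitivity for detecting a first cardiac arrest episode as primary endpoint, so each patient contributes at most one event. The sizing rests on these statements:

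- Incidence: "The presumed incidence of cardiac arrest events (as defined above) is expected to be 8% per year".
- Follow-up: "Given an expected median follow-up duration of 1.5 years". The section also says "Participants will wear the CardioWatch 287-3 for one to two years".
- True sensitivity: assumed to be 95%.
- Result: "a sample of approximately 200 patients is needed to achieve this sensitivity with a 95% Wilson confidence interval ranging from 74% to 99" per cent, described as a margin of error of ±12%.

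The section gives no expected number of events and no allowance for dropout, non-wear or unusable recordings.

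**The concern.** The precision of a sensitivity estimate depends on the number of events, not on the number of patients. The article leaves that number for the reader to work out, and there are two ways to do so. Working forward from patients, incidence and follow-up gives about 23–24. Working back from the printed interval gives about 18. A reader therefore cannot tell how many first events the final validation study expects, or whether the listed inputs are the ones that led to 200 patients. At stake is the stated precision of the primary endpoint; the conduct of the study is not affected.

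**Working it through.** **Inputs** (all from the DETECT-4b section): N = 200; incidence 0.08 per year; follow-up 1.5 years; sensitivity p = 0.95; two-sided 95% Wilson interval, z = 1.96.

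**Step 1. Expected first events.**

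- Linear: 200 × 0.08 × 1.5 = 24.0
- Compounded: 200 × (1 − 0.92^1.5) = 23.5
- Constant hazard: 200 × (1 − exp(−0.12)) = 22.6

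**Step 2. Wilson interval.** Centre = (p + z²/2n) / (1 + z²/n). Half-width = [z / (1 + z²/n)] × √(p(1−p)/n + z²/4n²).

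For n = 24 and p = 0.95:

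- Centre = (0.95 + 0.0800) / 1.1601 = 0.888
- Half-width = (1.96 / 1.1601) × √(0.001979 + 0.001667) = 0.102
- Interval: 78.6% to 99.0%

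**Step 3. Printed figure against nearby event counts.**

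| Basis | Wilson 95% interval | Half-width (points) |
|---|---|---|
| Printed in the article | 74% to 99% | 12 |
| n = 24, p = 0.95 | 78.6% to 99.0% | 10.2 |
| n = 23, p = 0.95 | 78.1% to 99.0% | 10.5 |
| 23 of 24 | 79.8% to 99.3% | just under 10 |
| 22 of 23 | 79.0% to 99.2% | 10.1 |
| n = 18, p = 0.95 | 75.0% to 99.2% | 12.1 |
| n = 17, p = 0.95 | 74.2% to 99.2% | 12.5 |
| **17 of 18** | **74.2% to 99.0%** | **12.4** |

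Seventeen of 18 reproduces all three printed numbers.

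**Step 4. Could another method give the printed figures at about 24 events?** No variant tried gives 74%, 99% and ±12 together.

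- Wilson with continuity correction, n = 24: 75.8% to 99.6% (±11.9)
- Wilson for 22 of 24: 74.2% to 97.7% (±11.8)
- Clopper-Pearson for 23 of 24: 78.9% to 99.9%

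**Step 5. What would 18 events require?** Any one of the following:

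- Fewer patients: 18 / 0.12 = 150, or 18 / 0.1131 = 159 under a constant hazard
- Shorter mean follow-up: 18 / (200 × 0.08) = 1.125 years
- Lower incidence: 18 / (200 × 1.5) = 6% per year
- A loss of events: 1 − 18/24 = 25%, or 1 − 18/22.6 = 20%

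**Step 6. Does it matter that 1.5 years is a median?** If everyone is followed for one to two years with a median of 1.5, the smallest possible mean is 1.25 years (half the patients at 1 year, half at 1.5). That extreme gives 200 × 0.08 × 1.25 = 20 events. Under a constant hazard it gives 100 × 0.0769 + 100 × 0.1131 = 19.0. The Wilson interval at p = 0.95 is 76.4% to 99.1% for 20 events and 75.7% to 99.1% for 19. Even the most lopsided follow-up only approaches the printed lower limit.

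**Step 7. Comparison with DETECT-1b.** There, 50 patients × 60% = 30 events, and 29 of 30 gives 83.3% to 99.4% with half-width 8.0 points. This is the printed result, with no hidden allowance. The same procedure in DETECT-4b leads to 23 of 24, not 17 of 18.

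**The case against.** The best defence is an allowance that was made but not printed. Eighteen is exactly 75% of 24, and a loss of about a quarter is plausible for a wristband worn for one to two years. The article condenses a fuller protocol, which may state the allowance. This stands as a possible explanation, so the figures may all be compatible once one more input is known. It does not rescue the sentence as written, which presents about 200 patients as following from the listed inputs, whereas those inputs reach the printed interval with about 150–160.

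It is also fair to say that the discrepancy is in the cautious direction. The stated inputs give a slightly narrower interval than the one promised.

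A reader might be tempted by three stronger conclusions. The document does not support them.

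- *The study fails because it cannot confirm sensitivity above 90%.* It is true that with 24 of 24 detected the Wilson lower limit is 24 / (24 + 3.84) = 86.2%. But DETECT-4b is sized for precision and sets no test or lower-limit threshold. The figure of >90–95% ("The goal is to achieve high sensitivity") is a programme aim in the Discussion. The phrase "specificity can likewise be confirmed with sufficient power" is about specificity and touches sensitivity only through one adverb.
- *The symmetric margin conceals the low lower limit.* It does not: 74% stands in the same sentence.
- *The sample is too small for the stated precision.* The reverse holds, as noted above.

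**Conclusion.** The point holds as an arithmetic inconsistency. The printed 74% to 99% (±12 points) belongs to about 18 first events, while the printed inputs give 22.6 to 24, with an interval of about 78% to 99% (half-width about 10 points). The lower limit is thus about 4 points lower than the inputs imply.

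This assumes that 8% per year is the rate of first qualifying events, that mean follow-up is close to the stated median, and that no allowance applies, since none is stated. An undeclared loss of about 20–25% of events would reconcile the figures. Severity is minor: the sample size is adequate for the stated precision, and no endpoint or analysis changes.

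**What to change.** State the expected number of first events in the DETECT-4b section, then do one of the following:

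- Restate the interval as about 78% to 99% (half-width about 10 points) for 23–24 events.
- State the loss or non-wear allowance that reduces 24 events to about 18, and keep 74% to 99%.

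Replace the wording "a sample of approximately 200 patients is needed to achieve this sensitivity" with a statement that about 200 patients allow sensitivity to be estimated with that precision. Sample size determines precision; it does not bring about a sensitivity.

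The cost is one recalculated figure or one added sentence. No extra patients are needed and the design does not change.
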